### Outcome measurement

A clinical research coordinator who is also a licensed nurse will evaluate the outcome variables as an assessor. He/she is supposed to be unaware of the group to which the subject is assigned.

#### Primary outcome

The primary outcome is the proportion of responders (PR) [26] defined as the proportion of participants who answer “yes” to more than half of the adequate relief questions during the treatment period. The adequate relief question is: After the last visit, have you had adequate relief of your stomach pain or discomfort?

#### Secondary outcomes

##### Nepean Dyspepsia Index - Korean version (NDI-K)

The Nepean Dyspepsia Index (NDI) was developed by Talley et al. [27] and has been reported as a reliable questionnaire to measure the severity of dyspeptic symptoms and quality of life [28, 29]. The Korean version of the NDI (NDI-K) was validated by Lee et al. [30]. The minimum clinically important difference of NDI is 10 points on the total scale [31]. The NDI-K consists of two categories (symptom-based questions and quality of life); in this study, we will use only symptom-based questions about the period, severity, and degree of distress of 15 symptoms at baseline and again after 4 weeks.

##### Functional Dyspepsia-Related Quality of Life (FD-QoL) questionnaire

The FD-QoL questionnaire is made up of four sections with a total of 21 questions regarding quality of life measured by a 5-point Likert scale (0: not at all or not applicable, 1: a little, 2: moderately, 3: quite a lot, and 4: extremely). The FD-QoL questionnaire is distributed into 5 items about diet, 4 items about daily activity, 6 items regarding emotion, and 6 items about social functioning. The questionnaire is known to be reliable and trustworthy for assessing the effect of dyspepsia on a patient’s overall quality of life [32]. The FD-QoL questionnaire will be administered at baseline and again after 4 weeks.

##### Numeric Rating Scale (NRS) for abdominal discomfort

Subjects will be asked to verbally rate the intensity of their abdominal discomfort after each MA-induced discomfort MRI run (CONT, TASK1, and TASK2). We will use a 0–100 Numeric Rating Scale (NRS), where 0 is labeled “no discomfort” and 100 is labeled “the most intense discomfort tolerable”.

##### Ways of Coping Questionnaire (WCQ)

We will use the WCQ, which is composed of 66 items and uses a 4-point Likert scale that was developed by Folkman et al. [33] and validated by Lundqvist et al. [34]. There are 8 coping strategies: (1) Confrontive coping, (2) Distancing, (3) Self-controlling, (4) Seeking social support, (5) Accepting responsibility, (6) Escape-avoidance, (7) Planful problem solving, and (8) Positive reappraisal. In the WCQ, these 8 areas are categorized into 2 groups (active coping and passive coping). The WCQ will be administered at baseline and again after 4 weeks.

##### Coping Strategies Questionnaire (CSQ)

The CSQ is made up of 48 items and uses a 7-point Likert scale validated by Franco et al. [35] to evaluate the coping strategy for pain or acupuncture treatment. The CSQ is distributed across 8 areas: (1) Catastrophizing, (2) Distractor behaviors, (3) Self-instructions, (4) Ignoring the pain, (5) Reinterpreting the pain, (6) Hoping, (7) Faith and praying, and (8) Cognitive distraction. These areas are classified as either adaptive coping or disadaptive coping. The CSQ will be administered at baseline and after 4 weeks.

##### Perception of bodily sensation (PBS)

We will apply the PBS questionnaire developed by Schneider et al. [36] at baseline to assess the response to the abdominal discomfort induced by MA. The level of perceived bodily sensation varies from person to person and might lead to different responses of brain activation. The questionnaire consists of 10 areas and uses a 6-point Likert scale where higher points indicate a more sensitive response. In our trial, the PBS plays an important role in analyzing the brain’s response to abdominal discomfort.

##### State-Trait Anxiety Inventory (STAI)

The STAI [37] is a questionnaire that evaluates anxiety as a psychological factor. It consists of 40 items: 20 items to assess the state of anxiety (anxiety triggered by a specific event), and 20 items to determine the trait of anxiety (anxiety derived from personal characteristics) according to a 4-point Likert scale. Higher scores indicate a higher degree of anxiety. Dyspeptic symptoms and anxiety are closely correlated [38, 39]. Therefore, the effect of acupuncture on anxiety will be evaluated. This measurement will be checked at baseline and again after 4 weeks.

##### Center for Epidemiological Studies - Depression Scale (CES-D)

The CES-D was developed by Radloff in 1977 and has been applied worldwide [40, 41]. It is both valid and reliable for assessing self-reported depression. The CES-D is composed of 20 areas; it uses a 4-point Likert scale where higher scores indicate more severe depression. Generally, a total sum score of more than 25 points indicates definite depression; more than 21 points is probable depression, while more than 16 points is possible depression. The CES-D will be evaluated at baseline and after 4 weeks to determine if there was an association between depression and the effects of acupuncture treatment.

##### Metabolomics

A metabolomics study will be performed to analyze the difference between (1) FD before and after acupuncture treatment and (2) the acupuncture and sham acupuncture groups. Blood and urine samples will be collected at baseline and after 4 weeks. After collecting the blood, the plasma will be isolated by centrifugation and stored in a −73 °C deep freezer. The urine samples will be inverted two or three times, pipetted into the cryo tubes, and stored in the deep freezer until the time of analysis. The sample will be analyzed by NMR and ultra-performance liquid chromatography quadrupole/time of flight mass spectrometry (UPLC-Q/TOF MS). After obtaining the NMR and MS data for blood and urine samples, the patterns and biomarkers for FD could be discovered using a multivariate statistical analysis.

### Sample size calculation

The sample size was calculated based on a previous study [42] and the opinions of an expert group. Considering the previous study and the fact that more than a 30 % difference is regarded as significant in clinical practice based upon expert opinions, we assume that 70 % of the participants in the acupuncture arm would achieve adequate relief for over half of the study period, while up to 35 % of those in the sham group would achieve such an outcome. We set the dropout ratio at 10 %, the level of significance at α = 0.05, and a power of 1-ß = 0.80. The sample size was estimated based on the following formula:$$ \mathrm{n}={\left({\mathrm{z}}_{\alpha /2}\sqrt{2\overline{p}\left(1-\overline{p}\right)}+\mathrm{z}\upbeta \sqrt{p_t\left(1-{p}_t\right)+{p}_c\left(1-{p}_c\right)}\right)}^2/{\left({p}_t-{p}_c\right)}^2 $$

assuming p_t_ = 0.7 (p_t_: the effect of the acupuncture group) and p_c_ = 0.35 (p_c_: the effect of the sham control group).

We also considered the recent trend of neuroimaging trials when calculating sample size. In fMRI studies that use approximately 90,000 voxels to estimate the BOLD signal indirectly, conventional power calculations are often meaningless. Therefore, most related studies determined less than 20 participants to be an adequate sample size [22, 43, 44] due to the high cost of fMRI examinations. Therefore, we have assumed 35 subjects in each group considering the global trend of increases in subjects to ensure that we obtain sufficient data for our analysis.

### Statistical analysis

A statistical analysis will be conducted by an independent statistician using SPSS 16.0 (SPSS Inc., Chicago, IL, USA). All continuous variables will be presented as means and SDs, and categorical variables will be shown as a number (%). All analyses will be based on the intention-to-treat principle using the last observation carried forward rule. The statistical significance level will be considered to be 0.05 (two-sided) with 95 % confidence intervals (CI). When continuous variables are compared between two groups, a two-sample *t*-test (parametric method) or Mann–Whitney *U* test (non-parametric method) will be used. The paired *t*-test (parametric method) or Wilcoxon signed ranks test (non-parametric method) will be used to compare continuous variables both before and after the treatment. When the variable is categorical, a chi-square test or Fisher’s exact test will be implemented. If there are statistically significant differences between groups, an analysis of covariance (ANCOVA) or logistic regression will be used.

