### Intervention

Detailed information regarding the acupuncture treatment is described in the form of the revised STandards for Reporting Interventions in Clinical Trials of Acupuncture (STRICTA) [18] listed in Table 1. Thirteen acupoints that are widely used to manage digestive symptoms are selected [19, 20]. The treatment will last for 20 minutes each visit, and a total of ten treatment session will be implemented, including two sessions during the MRI scanning.

**Table 1 Tab1:** Acupuncture treatment details based on the STRICTA 2010 checklist

Item	Detail
1. Acupuncture rationale	1a) Style of acupuncture
	- Manual acupuncture based on traditional meridian theory.
	1b) Reasoning for treatment provided, based on historical context, literature sources, and/or consensus methods, with references where appropriate
	- Manual acupuncture treatments based on the traditional meridian theory, clinical experience, and consensus by the experts in acupuncture and FD.
	1c) Extent to which treatment was varied
	- No additional acupoints allowed.
2. Details of needling	2a) Number of needle insertions per subject per session (mean and range where relevant)
	- Fixed 13 acupoints.
	2b) Names (or location if no standard name) of points used (uni/bilateral)
	- LI 4, ST36, LR3, PC3, SP4, and ST34 (bilateral) and CV12 (unilateral).
	2c) Depth of insertion, based on a specified unit of measurement or on a particular tissue level
	- From 5 to 30 mm.
	2d) Response sought (for example, de qi or muscle twitch response)
	- De qi sensation
	2e) Needle stimulation (manual, electrical)
	- Manual stimulation: needle rotation with thumb and index fingers at 3 Hz.
	2f) Needle retention time
	- Fifteen minutes.
	2 g) Needle type (diameter, length, and manufacturer or material)
	- A sterilized stainless steel needle (0.2 × 40 mm, Dongbang Acupuncture Inc., Ungcheon, Boryeong, Korea).
3. Treatment regimen	3a) Number of treatment sessions
	- Ten treatment sessions in both groups including two sessions during fMRI scanning.
	3b) Frequency and duration of treatment sessions
	- Twice weekly for 4 weeks plus additional two treatments during fMRI scanning (before and after treatment), 15 minutes for each session.
4. Other components of treatment	4a) Details of other interventions administered to the acupuncture group (moxibustion, cupping, herbs, exercises, lifestyle advice)
	- No other interventions during the study period allowed.

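### Last observation carried forward as the only missing-data rule lets a dropout's final answer decide the responder count and sets change to zero on six scales; the direction of bias is not determined

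*Protocol article*

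**What the plan says.** The Statistical analysis section of the protocol article fixes one rule: "All analyses will be based on the intention-to-treat principle using the last observation carried forward rule". It makes no exception for the responder endpoint and names no sensitivity analysis.

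Under Primary outcome, a responder is someone who says *yes* "to more than half of the adequate relief questions during the treatment period". The question is asked repeatedly and looks back over the latest interval: "After the last visit, have you had adequate relief of your stomach pain or discomfort". The number of askings is not given. Table 1 (item 3b) gives the schedule: "Twice weekly for 4 weeks plus additional two treatments during fMRI scanning (before and after treatment), 15 minutes for each session".

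The NDI-K is recorded for the "degree of distress of 15 symptoms at baseline and again after 4 weeks". The FD-QoL, WCQ, CSQ, STAI and CES-D have the same two time points in their own subsections.

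The Sample size calculation section puts the sham response rate at 35% at most. For the other arm it states: "we assume that 70 % of the participants in the acupuncture arm would achieve adequate relief for over half of the study period". That section also allows 10% dropout and sets 35 per group.

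**The concern.** Carrying an answer forward asserts relief, or its absence, in intervals on which the participant never reported. In an endpoint that counts answers, one early answer can then settle the whole classification. The trial has 70 participants and a single binary primary test, so a few people classified in this way can decide whether it is significant.

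On the two-time-point scales, the last observation for anyone without a week-4 value is the baseline value. The rule then assigns that person exactly zero change, and the t-tests or rank tests treat the filled value as if it had been measured. Any improvement common to both arms is diluted in proportion to each arm's dropout, so unequal dropout produces a group difference by itself.

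**Working it through.** **Inputs.** Sample size calculation section: response 0.70 vs 0.35, two-sided alpha 0.05, power 0.80, dropout 10%, 35 per group. Number of relief questions: not stated. The schedule gives 2 × 4 = 8 treatment visits plus 2 scan sessions, so 8 to 10 is assumed.

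**The plan's own figure.** The printed formula, with a mean proportion of 0.525, gives n = (1.96·√(2·0.525·0.475) + 0.842·√(0.7·0.3 + 0.35·0.65))² / 0.35² = 30.75, so 31 per group; 31/0.9 = 34.4, so 35. The sample size reproduces.

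**Primary outcome, counting.** With Q questions, a single *yes* at question d followed by dropout scores 1 + (Q − d) under the rule. This exceeds Q/2 when:
- Q = 8: d ≤ 4 (at d = 4, 5/8)
- Q = 9: d ≤ 5 (at d = 5, 5/9)
- Q = 10: d ≤ 5 (at d = 5, 6/10)

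One *yes* at question 1 of 8 becomes 8/8. In the other direction, *yes, yes, yes, no* and then dropout at question 4 of 8 scores 3/8, a non-responder with three *yes* answers out of four given.

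**Primary outcome, planned rates.** Let 10% drop out in each arm, let completers respond at 0.70 and 0.35, and let s be the share of dropouts carried as responders. The observed rate is 0.9·p + 0.1·s.

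| Dropouts carried as responders | Acupuncture | Sham | Difference | Power at 35 per arm |
|---|---|---|---|---|
| none in either arm | 0.63 | 0.315 | 0.315 | 76% |
| all in both arms | 0.73 | 0.415 | 0.315 | 77% |
| all in acupuncture, none in sham | 0.73 | 0.315 | 0.415 | 95% |
| none in acupuncture, all in sham | 0.63 | 0.415 | 0.215 | 44% |
| same rates as completers | 0.70 | 0.35 | 0.35 | 85% |

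The extremes lie 10 points either side of 0.315, the value when both arms' dropouts are classed alike.

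**Primary outcome, observed counts.** Ten percent of 35 is 3.5, so 3 to 4 per arm; 4/35 = 11.4 points. Illustrative counts, Pearson chi-square:
- 20/35 vs 13/35: p = 0.094
- four acupuncture dropouts carried as *yes*, 24/35 vs 13/35: p = 0.008
- four in each arm, 24/35 vs 17/35: p = 0.089
- four in sham only, 20/35 vs 17/35: p = 0.47

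Two added acupuncture responders are enough to cross 0.05 with Pearson (22/35, p = 0.031), and three with Fisher's exact test (23/35, p = 0.031).

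**Two-time-point scales.** The mean change in an arm with dropout fraction d is (1 − d) × the completers' mean change. With d = 10% in both arms, a true 10-point difference is estimated as 0.9 × 10 = 9. With 10 points of improvement in both arms and dropout of 15% vs 5% (assumed), the estimates are 8.5 and 9.5, a false difference of 1 point.

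**The case against.** Several points on the other side stand.

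- **Direction.** A reader might infer that the rule manufactures responders and so favours acupuncture. The documents do not support that: a last *no* manufactures non-responders just as readily, and nothing is known about arm-specific dropout or last answers. If dropouts respond like completers, the difference stays at 0.35.
- **Size.** The move from p = 0.094 to p = 0.008 is a worst case. It needs all four acupuncture dropouts to be carried as *yes* and none in sham. With four added in both arms, p hardly changes.
- **Contradiction.** A reader might say the rule contradicts the endpoint definition. That is too strong. One section defines the endpoint and the other says how gaps are filled, and every imputation method supplies answers not given. The number of questions is also an assumption here.
- **Scales.** The bias at planned dropout is modest. The false 1-point difference rests on an assumed dropout imbalance and is a tenth of the 10-point minimum important difference that the protocol quotes for the NDI; equal dropout only shrinks the effect.
- **Imaging and spectra.** Read literally, the word *all* would carry baseline scans and spectra to week 4. That reading is strained: both have their own processing sections and software, and the metabolomics section refers to samples actually collected.
- **The remedy.** Treating an unanswered question as not *yes* is also a fixed fill-in. If true response is 50% in both arms, dropout is 15% vs 5% and dropouts leave before qualifying, the rates become 0.85 × 50 = 42.5% and 0.95 × 50 = 47.5%, a false 5-point difference.

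None of this makes carry-forward sound as the only rule. The rule is stated in the text, so it is not a detail left to an analysis plan.

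**Conclusion.** The concern holds, at should-fix level. As the sole rule, carrying forward makes the primary classification of a dropout depend on when that person left and on one last answer. At the planned 10% dropout the group difference can move by up to about 10 points either way in the worst case, enough to cross 0.05 in a trial of this size. The sign of the bias cannot be determined from the documents. For the NDI-K, FD-QoL, WCQ, CSQ, STAI and CES-D the rule is baseline carried forward: a difference shrinks by the dropout fraction when dropout is equal, and a small spurious difference appears when it is not. The PBS, taken at baseline only, is not affected.

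This rests on 8 to 10 relief questions (assumed), on carry-forward being applied answer by answer, and on dropout near the planned rate. The sample size calculation is not in error. It does, however, treat dropouts as lost (31 evaluable per arm), whereas the analysis section keeps all 35 with filled values.

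**What to change.** Replace the carry-forward rule in the Statistical analysis section.

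- **Primary outcome.** Analyse all randomised participants. The denominator is the number of scheduled relief questions, which should be stated, and an unanswered question is not a *yes*. Add multiple imputation of visit-level answers by arm as a sensitivity analysis, because the fixed fill-in can itself mislead when dropout differs between arms. Carry-forward may be kept as a further sensitivity analysis if wanted.
- **Two-time-point scales.** Use multiple imputation by arm followed by ANCOVA adjusted for the baseline score, in place of carry-forward.

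The cost is protocol wording and some programming; no data collection changes. The downside should be stated openly: response rates will be lower in both arms. If all 10% of dropouts count as non-responders and completers respond at 70% and 35%, the comparison is 63% vs 31.5%. Power at 35 per arm is then about 76%, below the planned 80%, and 39 per arm would be needed to restore it.

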## Methods/design

### Objectives

The aims of this study are as follows:Investigate whether manual acupuncture brings adequate relief of FD symptoms in comparison with the sham control group.Determine the difference of brain activity between the real and sham acupuncture groups and the correlation between brain and clinical outcomes.Assess any correlation between differences and changes in the metabolite and clinical outcomes.

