### Hypothesis

We hypothesized that 10 sessions (4 weeks) of acupuncture treatment will improve FD symptoms, and a mechanistic difference will exist between the acupuncture and the sham control for FD based upon the fMRI and the metabolomics study.

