#### Inclusion criteria

The inclusion criteria are as follows:Age between 30 and 49 years.Meeting the definition of FD and postprandial distress syndrome (PDS) as a subtype of FD according to the Rome III criteria [17].Complaints of a degree of dyspepsia that produces a score of more than 40 points on the visual analog scale (VAS; 0, no symptom at all; 100, the most severe symptom one has ever had).Answer at least three questions worth more than 2 points on the Gastrointestinal Impact Scale.Have normal esophagogastroduodenoscopy results within a year and no evidence of any organic diseases.Individuals who are not supposed to take any other treatments associated with FD during the study.

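### Within-arm before-after tests on the continuous secondary outcomes are planned as significance tests, not labelled descriptive, and cannot show an effect of acupuncture over sham

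*Protocol article*

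**What the plan says.** The Statistical analysis section sets a two-sided 0.05 level for the trial. It then gives two kinds of test for continuous outcomes. The first is between arms: "When continuous variables are compared between two groups, a two-sample" t-test or a Mann–Whitney test. The second is a paired t-test or Wilcoxon signed ranks test, which "will be used to compare continuous variables both before and after the treatment". Neither kind is ranked above the other, and the paired tests are not called descriptive. ANCOVA or logistic regression follows only if groups differ significantly.

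The Hypothesis section has two halves. The clinical half is that "10 sessions (4 weeks) of acupuncture treatment will improve FD symptoms", with no comparator. The mechanistic half does name one: "a mechanistic difference will exist between the acupuncture and the sham control". Objective 1 is comparative on the clinical side too: "Investigate whether manual acupuncture brings adequate relief of FD symptoms in comparison with the sham control group".

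The Metabolomics section lists two contrasts. The first is "1) FD before and after acupuncture treatment" and the second is acupuncture against sham. Entry requires dyspepsia that gives "a score of more than 40 points on the visual analog scale".

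Six secondary scales are measured at baseline and after 4 weeks, and so fall under the paired tests: NDI-K, FD-QoL, WCQ, CSQ, STAI and CES-D.

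**The concern.** Randomisation protects only the comparison of acupuncture with sham. A paired test within one arm asks whether the mean changed, and several things other than the needle can change it: the passage of time, expectation and contact with the practitioner. For symptom scores there is also regression to the mean, because participants enter on high symptoms. The plan itself expects up to 35% responders under sham, so some shared improvement is anticipated.

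As worded, the clinical half of the hypothesis would be satisfied by a significant paired test in the acupuncture arm alone. Two misreadings would then be open for the secondary outcomes. One takes a significant improvement after acupuncture as efficacy. The other takes significance in the acupuncture arm but not in the sham arm as a difference between arms. Both can arise often when the arms do not differ at all.

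**Working it through.** **The plan's own figure.** The Sample size calculation section uses responder rates of 0.70 and 0.35, two-sided α = 0.05 and power 0.80. With mean rate 0.525:

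n = (1.960 × √(2 × 0.525 × 0.475) + 0.8416 × √(0.70 × 0.30 + 0.35 × 0.65))² / 0.35² = 30.75, so 31 per arm.

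Allowing for 10% dropout, 31 / 0.9 = 34.4, so 35 per arm. The stated figure reproduces. It rests on the between-arm responder comparison and does not involve the paired tests.

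**Inputs for the check.**
- n = 35 per arm (Sample size calculation), with 31 as the number left after dropout.
- Two-sided 0.05 level (Statistical analysis).
- No true difference between acupuncture and sham.
- The same mean improvement in both arms, d, in SDs of the change score. The article gives no SD or expected change for any continuous outcome, so d is an assumption, shown from 0.2 to 0.8.

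**Formulas.** The paired t statistic follows a noncentral t distribution with n − 1 degrees of freedom and noncentrality d√n. Let p be the probability that it exceeds the two-sided critical value (2.032 for n = 35). The arms are independent, so the probability of significance in the acupuncture arm only is p(1 − p).

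**Results, no difference between arms.**

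| d | n = 35: acupuncture arm significant | n = 35: acupuncture only | n = 31: acupuncture arm significant | n = 31: acupuncture only |
|---|---|---|---|---|
| 0.2 | 21% | 17% | 19% | 15% |
| 0.3 | 41% | 24% | 37% | 23% |
| 0.35 | 52% | 25% | 47% | 25% |
| 0.5 | 82% | 15% | 77% | 18% |
| 0.8 | 99.6% | 0.4% | 99% | 0.9% |

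For d = 0.35 and n = 35, the noncentrality is 0.35 × √35 = 2.07 and p = 0.521, so p(1 − p) = 0.521 × 0.479 = 0.250. That is the ceiling, since p(1 − p) cannot exceed 0.25.

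**Comparison.** A two-sample t-test on change, simulated over 20,000 trials with 35 per arm, rejected in 5.0% to 5.1% of trials at d = 0.3, 0.5 and 0.8. Half of the nominal 5%, or 2.5%, falls in favour of acupuncture, whatever the shared improvement.

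The two misreadings behave differently as d grows. The acupuncture-only pattern peaks near d = 0.35 and almost vanishes by 0.8. A significant before-after change in the acupuncture arm becomes nearly certain.

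**The case against.** The strongest reply is that the article defines efficacy against sham almost everywhere else: in the Abstract, in objective 1 and in the Discussion. The second half of the hypothesis names sham as well. Between-arm tests for continuous outcomes are already planned and are listed before the paired ones. No sentence says that efficacy will be read from significance in one arm and not the other. On this view the paired tests are routine reporting, and the harm is a possible later misreport.

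Much of this stands, and it rules out several stronger inferences that a reader might draw:

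- **That the main efficacy result is exposed.** It is not. The primary outcome is a responder proportion, powered between arms and covered by the chi-square or Fisher test.
- **That the trial tests a before-after efficacy hypothesis.** Read with objective 1, the clinical half is loose wording that does not match the objective.
- **That every continuous measure is affected.** The PBS questionnaire is taken at baseline only. The analysis described for the metabolomic spectra is multivariate (PCA, PLS-DA or OPLS-DA), so the percentages above do not describe it.
- **That all scores regress to the mean.** The entry threshold is a dyspepsia VAS, which is not itself a listed outcome. The argument is plausible for symptom scores such as NDI-K. For anxiety, depression and coping scales it depends on an unstated correlation with that VAS.
- **That 25% is a typical error rate.** It is the mathematical maximum.

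The reply does not remove the point. The article states the paired analysis as a significance test, and no rule says which test governs the conclusion when the two disagree.

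**Conclusion.** The point holds for the six scales measured at baseline and week 4. Their within-arm p-values do not test acupuncture against sham, yet the plan presents them as tests beside a clinical hypothesis that names no comparator. The error from relying on them could be large: over shared improvements of 0.2 to 0.8 SD, the acupuncture arm alone would reach significance in up to a quarter of trials, and the before-after test in that arm would be significant in 21% to 99.6%. These figures assume no real-sham difference, equal improvement in both arms, normally distributed change scores and 35 analysed per arm; d is not taken from the documents.

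The primary analysis and the sample size are untouched, and valid between-arm tests are already planned. Severity is minor to moderate.

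**What to change.** 1. In Statistical analysis, report within-arm change descriptively, as mean change with SD or confidence interval and no p-value.
2. For NDI-K, FD-QoL, WCQ, CSQ, STAI and CES-D, base conclusions on the between-arm comparison of the week-4 value by ANCOVA adjusted for the baseline value of the same scale. Run it for all six, not only after a significant difference has been found.
3. Keep the metabolomic before-after contrast as exploratory, and let any mechanistic claim rest on acupuncture versus sham. The multivariate methods need not be replaced.
4. Word the clinical half of the hypothesis as improvement in FD symptoms compared with sham, to match objective 1.

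The cost is wording and a little analysis. The baseline values are already collected, and no visits or participants are added.
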